#### Evaluation of Intervention Feasibility

The feasibility of the system will be examined by evaluating objective (ie, the pattern of interaction with the exercises) and subjective (ie, participant ratings and experience with the exercises) engagement behavioral patterns.

#### Evaluation of the Distal Outcomes of the Intervention

ER skills and level of distress (ie, stress as well as anxiety and depressive symptoms) will be evaluated before and after the intervention period for the purpose of safety monitoring and to inform the design of a follow-up RCT. In terms of safety, the results will be used to indicate whether negative changes in individuals’ MH (ie, distress symptoms) occurred between baseline and the end of the intervention period. As there is no comparator group, the results will provide only an indication of a potential link between worsened (or improved) distress symptoms and the intervention, which will be further tested in a traditional RCT. In terms of RCT design, given the innovative nature of this intervention, there is no prior data available to estimate its effect size. Therefore, we will use the pre-post evaluation of distal outcomes in this study as a pilot evaluation of changes in the distal outcomes to estimate the potential effect size of the intervention. This estimate will be used to calculate the sample size for the standard RCT, where between-group changes in distal outcomes (ie, ER skills and distress symptoms) will be evaluated.

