**Figure 1 figure1:**
[figure not shown]
CONSORT (Consolidated Standards of Reporting Trials) flow diagram of participants’ progress through the mixed methods study integrating a microrandomized trial with semistructured interviews. EMA: ecological momentary assessment.

**Table 1 table1:** Overview of measurements performed during phase 1 (microrandomized trial).

	Day 1	Day 2 to day 22	Day 23
Emotional states		✓	
Thought believability and discomfort^a^		✓	
Demographics	✓		
Experience with MH^b^ apps	✓		
Knowledge of approaches	✓		
Use of MH techniques	✓		✓
Ten-Item Personality Inventory	✓		
General Health Questionnaire-12	✓		
Patient Health Questionnaire-9^c^			✓
Generalized Anxiety Disorder-7	✓		✓
Perceived Stress Scale-14	✓		✓
Emotion Regulation Skills Questionnaire	✓		✓

^a^Thought believability and discomfort are measured only before and after the cognitive defusion exercises.

^b^MH: mental health.

^c^The Patient Health Questionnaire-9 is part of the eligibility screening questionnaire; it is not readministered at baseline.

In phase 2, semistructured interviews will be conducted with a subsample of participants (21/200, 10.5%) investigating their user experience. The results of the qualitative phase will be used to interpret the quantitative results, obtaining a well-rounded picture of how the mobile intervention is functioning and its feasibility.

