##### Eligibility Criteria

Participants are eligible to participate in our study if they are currently enrolled at EUR, are aged between 18 and 27 years, own a smartphone with an active phone number, feel comfortable speaking and writing in English, and score between 5 (mild symptoms) and 19 (moderately severe symptoms) on the Patient Health Questionnaire-9 (PHQ-9) [61]. The last criterion was selected to ensure that participants in the study experience a certain degree of MH problems, thereby making the interventions in the app more relevant to them and allowing for the observation of intervention impact within a population that is likely to derive the greatest benefit from it. Participants who have experienced significant suicidal thoughts over the past month; have a medical diagnosis of psychosis or bipolar disorder, severe clinical depression, or anxiety disorder; or are undergoing psychopharmacological treatment or treatment with experimental drugs are ineligible for this study.

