## Discussion

### Overview

This study will investigate the effectiveness and feasibility of digitally delivered therapeutic exercises designed to facilitate adaptive ER among university students. A secondary goal of this study focuses on the evaluation of distal outcomes, that is, changes in ER skills and distress symptoms as a result of the intervention, which will serve as a safety indicator and inform the sample size estimation of the RCT to follow. In addition, contextual moderators that could be relevant for the recommendation system that will link students to exercises relevant to their needs and preferences will be explored.

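### The uncontrolled pre-post change in the distal outcomes is to serve as the effect size for a between-group RCT; it is likely to overstate that effect and risks an underpowered RCT

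*Protocol article*

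**What the plan says.** Under Study Objectives, the section Evaluation of the Distal Outcomes of the Intervention states that no earlier data exist from which to estimate an effect size, and continues: "we will use the pre-post evaluation of distal outcomes in this study as a pilot evaluation of changes in the distal outcomes". It then fixes the purpose: "to estimate the potential effect size of the intervention. This estimate will be used to calculate the sample size for the standard RCT", a trial in which between-group changes will be evaluated. The Overview of the Discussion repeats the commitment. It says of the distal changes: "which will serve as a safety indicator and inform the sample size estimation of the RCT to follow".

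The same objectives section concedes the missing control: "As there is no comparator group, the results will provide only an indication of a potential link" between the intervention and a change in distress. That caution is attached to the safety reading and to later testing. It is not carried over to the sample size.

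Two further statements matter for the PHQ-9. The Eligibility Criteria require that participants "score between 5 (mild symptoms) and 19 (moderately severe symptoms) on the Patient Health Questionnaire-9". Footnote c of Table 1 adds: "The Patient Health Questionnaire-9 is part of the eligibility screening questionnaire; it is not readministered at baseline". The Secondary Outcomes section confirms that one PHQ-9 score serves both for screening and as the baseline depression level.

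**The concern.** The follow-up RCT will estimate the change in the app arm minus the change in a control arm. The figure meant to size it is the change in one arm only. Whatever a control arm would also have experienced over three weeks stays in that figure, including natural course and non-specific effects of taking part in a study.

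For the PHQ-9 there is a further component. Participants enter because their screening score lies in a window, and that same score is subtracted from the day 23 score. Measurement error and short-term fluctuation that helped someone to qualify are not expected to persist, so the group mean can move with no intervention effect at all. The GAD-7, PSS-14 and Emotion Regulation Skills Questionnaire are not selected on directly and are affected only through their correlation with the PHQ-9.

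The design offers no way to remove these components. Microrandomization gives each participant a mix of exercises and health snippets, so it supplies no unexposed group for the day 23 outcomes. The regression planned under Secondary Outcome Analysis adjusts for covariates, including the number of completed exercises, but has no control arm. At stake is the size of the next trial.

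**Working it through.** **Plan's own figure.** There is none to reproduce. The article gives no effect size, SD, alpha, power or sample size for the follow-up RCT. Everything below illustrates the consequence on assumed inputs.

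**Step 1. Regression to the mean from the PHQ-9 window.**

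From the article: the 5 to 19 window, the 0 to 27 scale, and the screening score as baseline. Assumed: source SD 5, retest correlation r from 0.6 to 0.85, no treatment effect, the same population mean at both times. Scores were simulated as correlated pairs, rounded and limited to 0-27, and kept if the first score was 5 to 19. Apparent improvement d = (mean first score − mean second score) / SD of the selected first scores. Two shapes were used, because a non-negative symptom score need not be normal.

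| Source mean | Normal shape, d (r 0.85 to 0.6) | Right-skewed (gamma) shape, d (r 0.85 to 0.6) |
|---|---|---|
| 6 | 0.14 to 0.36 | 0.10 to 0.29 |
| 7 | 0.11 to 0.28 | 0.07 to 0.19 |
| 8 | 0.08 to 0.21 | 0.04 to 0.11 |
| 9 | 0.06 to 0.15 | 0.01 to 0.04 |
| 11 | 0.02 to 0.05 | −0.02 to −0.05 |

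One cell worked out: normal shape, mean 7, r = 0.6. The selected group falls by 0.94 points with a baseline SD of 3.32, so d = 0.94 / 3.32 = 0.28.

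At source means of 6 to 8 the range over both shapes is 0.04 to 0.36. At 9 to 11 it shrinks, and with a skewed distribution it is near zero or slightly reversed, because the window cuts the upper tail as well as the lower one.

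**Step 2. What an inflated d does to an RCT.**

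Assumed: two-sided alpha 0.05, 80% power, equal allocation. Per arm, n = 2(1.96 + 0.8416)² / d² = 15.70 / d². Power at the true effect is approximately Φ(d_true × √(n/2) − 1.96).

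Take a true between-group d of 0.3, and let the pre-post d exceed it by the change not caused by the intervention.

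- Excess 0: n = 15.70 / 0.09 = 174.4, so 175 per arm. Power 80%.
- Excess 0.1, planned d 0.4: n = 15.70 / 0.16 = 98.1, so 99. Power = Φ(0.3 × √49.5 − 1.96) = Φ(0.15) = 56%.
- Excess 0.2, planned d 0.5: n = 15.70 / 0.25 = 62.8, so 63. Power = Φ(0.3 × √31.5 − 1.96) = Φ(−0.28) = 39%.
- Excess −0.1, planned d 0.2: n = 15.70 / 0.04 = 392.4, so 393. The RCT would be larger than needed.

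The excess values are chosen for illustration and are not estimated from this study. They show that 0.1 SD is enough to matter.

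**The case against.** The strongest reply is that the article is modest about this estimate. It calls the exercise a pilot, speaks of a potential effect size, admits the missing comparator, and in the Discussion says only that the changes will inform the sample size. The wording is indeed hedged. But the objectives section then makes the estimate the input to the sample size calculation, with no discount, lower confidence limit or external anchor.

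A second reply concerns direction. A reader might infer that the follow-up RCT will be too small. The documents do not support that certainty. They give no sample size for it, and Step 1 shows that regression to the mean under a two-sided window depends on a source distribution that they do not report. Some features may also shrink the pre-post change relative to the later effect: exercises come at 60% of decision points, the PSS-14 asks about the past month although the intervention lasts 21 days, and the RCT will test an optimized app. This stands, and it limits the point to a likely overstatement and a risk.

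Two further inferences should not be drawn. One is that the mean change, used as the safety indicator, would hide real worsening. The objectives section speaks of negative changes in individuals and does not fix the mean as the indicator. The other is that repeated self-rating is a bias to be removed. The momentary assessments, 42 before and 42 after, are a core feature of the app, so their effect belongs to the intervention unless the RCT's control arm also completes them, which is not stated.

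Finally, nothing in this trial's own randomization, primary analysis or sample size is touched. That is correct; the consequence falls on the next trial.

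**Conclusion.** The point holds as a flaw in a stated objective. A single-group pre-post change is not an estimate of the between-group difference that the RCT will test, and the article commits to using it as one while acknowledging that there is no comparator. The PHQ-9 is the most exposed outcome, because the selecting score is also the baseline.

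The likely direction is overstatement of the effect and hence an underpowered RCT. On the assumed inputs above, selection on the PHQ-9 alone contributes about 0.04 to 0.36 SD at source means of 6 to 8, and about zero or slightly negative values at 9 to 11 with skewed scores. An excess of 0.1 or 0.2 SD over a true d of 0.3 lowers power from 80% to about 56% or 39%. These figures rest on an assumed source mean, SD, retest correlation and true effect; the documents give none of them. If the sign of the bias is uncertain too, that does not rescue the plan, since the RCT would then be sized wrongly in an unknown direction. The change should be made, and there is still time: data collection has ended, but the analyses are under way and the RCT lies ahead.

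**What to change.** In the objectives section on distal outcomes and in the Discussion overview:

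- State that the pre-post change will not be used as the effect size for the RCT.
- Use this study for what one arm can supply: the SDs of the distal outcomes, the baseline to day 23 correlations, attrition and engagement.
- Take the RCT difference from a smallest worthwhile difference or from controlled evidence. The article's own sample size section already draws on results of internet interventions in university students.
- Report the pre-post PHQ-9 change beside a range for regression to the mean, with the assumed source mean, SD and retest correlation stated.

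The cost is a few sentences and one added calculation; no new data are needed. The downside is that the later RCT may turn out larger than hoped.

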#### Exploratory Goal: The Impact of Contextual Moderators on Proximal Intervention Effects

The role of the time of day, momentary emotional state, personality type, preferences, and intervention type as moderators will be explored to determine the context under which the intervention and its categories exercises are the most effective.

## Methods

### Study Design

This study uses an explanatory sequential mixed methods approach combining an MRT (phase 1) [22] with follow-up semistructured interviews (phase 2; refer to Figure 1 for an overview). During the MRT, the participants (N=200) will be randomized 2 times per day (morning and evening) to the intervention (ie, an exercise supporting ER; 60% probability) or to a control intervention (ie, a health snippet; 40% probability) over a span of 21 days. Data will be collected at baseline and at the end of the 3-week intervention period, as well as daily via the app before and after the completion of each assigned exercise or health snippet. The primary outcomes include changes in emotional states and engagement patterns with the intervention. For the exercises targeting unhelpful thoughts, differences in thought believability and discomfort before and after the CD exercises will be evaluated. The secondary outcomes include changes in the 4 distal outcomes—ER skills, perceived stress level, and levels of anxiety and depressive symptoms—which will be measured at baseline and at the end of the intervention phase (ie, after 21 days; refer to Table 1 for the measurement schedule).

**Figure 1 figure1:**
[figure not shown]
CONSORT (Consolidated Standards of Reporting Trials) flow diagram of participants’ progress through the mixed methods study integrating a microrandomized trial with semistructured interviews. EMA: ecological momentary assessment.

**Table 1 table1:** Overview of measurements performed during phase 1 (microrandomized trial).

	Day 1	Day 2 to day 22	Day 23
Emotional states		✓	
Thought believability and discomfort^a^		✓	
Demographics	✓		
Experience with MH^b^ apps	✓		
Knowledge of approaches	✓		
Use of MH techniques	✓		✓
Ten-Item Personality Inventory	✓		
General Health Questionnaire-12	✓		
Patient Health Questionnaire-9^c^			✓
Generalized Anxiety Disorder-7	✓		✓
Perceived Stress Scale-14	✓		✓
Emotion Regulation Skills Questionnaire	✓		✓

^a^Thought believability and discomfort are measured only before and after the cognitive defusion exercises.

^b^MH: mental health.

^c^The Patient Health Questionnaire-9 is part of the eligibility screening questionnaire; it is not readministered at baseline.

In phase 2, semistructured interviews will be conducted with a subsample of participants (21/200, 10.5%) investigating their user experience. The results of the qualitative phase will be used to interpret the quantitative results, obtaining a well-rounded picture of how the mobile intervention is functioning and its feasibility.

### Participants

#### Phase 1: MRT

##### Overview

A total of 200 students at EUR will be recruited. A web-based sample size calculator for MRT studies [57,58] was used to calculate the sample size based on the duration of the intervention period (21 days), expected availability intervention randomization probability (60%), and proximal treatment effect. We expect that participants will respond to approximately 70% of the prompts throughout the intervention period (ie, we assume a constant availability of 70%). Furthermore, we assume a linear effect of the intervention on the proximal outcome measures over time with an average size of 0.1 and an initial effect of 0 at the start of the study. In comparison with the large effect size for in-person therapy based on transdiagnostic approaches to emotional disorders [59], we assume a smaller effect size for our study, which is in line with the results of internet interventions for MH in university students [27] and with a similar MRT study protocol examining an ACT intervention [54]. On the basis of these assumptions, 126 participants will generate 80% power to detect the assumed effect with a significance level of .05. We will increase the participant number to 200 to account for a dropout rate of 40%, in line with average attrition rates for MH interventions delivered through smartphones [60].

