#### Primary Outcome Analysis

##### Effects of the Intervention on the Proximal Outcomes

The weighted and centered least squares method developed by Boruvka et al [105] to evaluate data from MRT studies will be used to estimate and test the causal excursion effects of the intervention on the proximal outcomes. This method assesses parameters in treatment effect models and allows for the inclusion of covariates that can reduce the variance of the treatment effect estimates. Similar to generalized estimating equations and multilevel models, this method can effectively manage nested data (ie, decision points nested within participants) and within-person dependencies across time in the outcome. A detailed explanation of the analyses is available in Multimedia Appendix 4 [23,51,105,106].

As a primary goal of this study, we will test the overall (average, across all decision points) effect of engaging in any intervention versus engaging in the control intervention on the emotional states measured with the postintervention EMA upon intervention completion. Furthermore, we aim to evaluate whether this effect deteriorates over time by estimating the interaction between the overall intervention effect and the day in the study.

As a subgoal, we will examine differences in the overall effect of engaging in a suggested intervention versus engaging in the control intervention on emotional states for each intervention category separately. We will control for the pretreatment scores of positive and negative affect measured by the preintervention EMA across all models. To account for repeated dependent measures, robust SEs will be calculated using a sandwich estimator, and because we are comparing multiple outcomes, the results will be controlled for multiple testing using Bonferroni correction, that is, we will divide the α value by the number of comparisons being made (ie, 2; hence, we will use α=.025).

Data may be missing if participants do not complete the EMAs before and after an exercise because without the completion of both measurements the observation for the proximal outcome will be missing. If no more than 10% of the data are missing, our primary analysis will be performed as a complete case analysis. If >10% of data are missing, the missing data will be handled by using multiple imputation approaches and outcome models averaged across imputations to adhere to the intention-to-treat principle.

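### The 80% power for 126 participants is stated at α=.05, but each affect outcome is tested at α=.025, where power is never given and comes to about 71% to 81% depending on the test assumed

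*Protocol article*

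**What the plan says.** The power statement is in the protocol article under Participants, Phase 1: MRT, Overview. It rests on a web-based calculator for microrandomized trials, with a 21-day period, constant availability of 70%, a 60% probability of receiving an exercise, and a linear effect with "an average size of 0.1 and an initial effect of 0 at the start of the study". It concludes that "126 participants will generate 80% power to detect the assumed effect with a significance level of .05". Recruitment is then raised to 200 to allow for 40% dropout.

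Under Effects of the Intervention on the Proximal Outcomes, the primary goal is to "test the overall (average, across all decision points) effect" of exercise against control. The same section says that "because we are comparing multiple outcomes, the results will be controlled for multiple testing using Bonferroni correction", and specifies: "we will divide the α value by the number of comparisons being made (ie, 2; hence, we will use α=.025". The section on momentary emotional states defines two composite outcomes, positive affect and negative affect, which accounts for the divisor of 2.

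**The concern.** The sample size and the analysis use different significance levels, and the article does not connect them. The power figure is given "with a significance level of .05"; the analysis section gives "ie, 2; hence, we will use α=.025". A smaller α lowers power at a fixed sample size, so the stated 80% at .05 cannot be carried over to the planned test.

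The test may differ as well. A linear effect starting at 0 is the kind of shape for which a two-parameter time-varying test is used, whereas the primary analysis names a single average over all decision points. The article does not say which test the calculator ran.

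What is at stake is how a null result is read. Analysis was still under way when the article appeared. A non-significant result on either affect outcome would be set against a power figure that does not describe the test performed.

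**Working it through.** **Inputs from the article**
- Decision points: 2 per day for 21 days = 42 (Study Design)
- Availability: 0.70, constant (Overview of Phase 1: MRT)
- Randomization probability: 0.60, so 0.6 × 0.4 = 0.24
- Average effect: 0.1, initial effect 0, linear
- Stated result: N = 126, power 80%, α = .05
- Analysis α: .025 per outcome

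**Assumptions, because the article does not state them:** the test is two-sided, the 0.1 is standardized, and both daily decision points were entered in the calculator.

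**Method.** Non-central F test with p and N − q − p degrees of freedom, where p is the number of effect parameters and q the number of nuisance parameters. Taking q as 1, 2 or 3 moves N by at most one. The non-centrality is N × 0.7 × 0.24 × Σd², where d is the effect at each decision point.

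- Average effect (p = 1): Σd² = 42 × 0.1² = 0.42, so 0.7 × 0.24 × 0.42 = 0.0706 per participant. At N = 126 the non-centrality is 8.89.
- Linear effect (p = 2), rising by 0.01 per day over days 0 to 20: Σd² = 2 × 0.0001 × 2870 = 0.574, so 0.7 × 0.24 × 0.574 = 0.0964 per participant. At N = 126 the non-centrality is 12.15.

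**Step 1: attempt to reproduce 126 at α=.05**

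| Test | N for 80% power | Power at N = 126 |
|---|---|---|
| Average effect, 1 df | 114 | 84% |
| Linear, 2 df | 103 | 88% |

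Neither returns 126 or 80%. An N of 126 at .05 appeared only for effect shapes that the article does not describe, such as a linear rise to a plateau at about day 5.

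**Step 2: the same tests at α=.025**

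| Test | N for 80% power | N = 120 | N = 126 | N = 137 |
|---|---|---|---|---|
| Average effect, 1 df | 138 | 74% | 76% | 80% |
| Linear, 2 df | 123 | 79% | 81% | 85% |

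Here 120 is 200 less 40%, and 137 is the number reported to have completed phase 1.

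**Step 3: accept the stated 80% at .05 and change only α.** By the normal approximation, 1.960 + 0.842 − 2.241 = 0.560, and Φ(0.560) = 0.71. Power is 71%.

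**Step 4: the dropout allowance.** 126 / (1 − 0.40) = 210, not 200. At the planned dropout, 200 recruits leave 120, which is below the 126 on which the power statement rests.

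**The case against.** The strongest reply is that, under the effect shape the article names, there is no shortfall. A two-degree-of-freedom linear test with 126 participants has 81% power at α=.025 and needs only 123 for 80%. The 126 may therefore have been calculated at .025 and reported as .05. That is possible and cannot be confirmed from the article. If it is so, the printed .05 is wrong and the paragraph still needs correction.

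A second reply is that the 76% depends on inputs the article does not state, and that neither the calculator nor the appendix on the analytic method is shown. This stands, and it is why a range is given.

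A third is that the correction sentence sits in the paragraph on intervention categories. Its reason is multiple outcomes, however, and its divisor of 2 fits the two affect composites and not the five categories, so it applies to the primary test too.

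Three stronger readings are tempting, and the article does not support them:
- **That the change in α costs the difference between 80% and 76%.** Those figures come from two different calculations. Within the average-effect formula the drop is from 84% to 76%; from the stated figure it is from 80% to 71%.
- **That an effect assumed to start at 0 and grow contradicts the plan to test whether it deteriorates.** There is tension, but the linear shape is a planning assumption, and the estimated interaction with study day can take either sign.
- **That the completed trial is underpowered.** The 137 completers give about 80% for the average-effect test at .025. Of the 161 who took part, those who did not complete may still contribute observed decision points; all 161 would give 86%.

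**Conclusion.** The point holds as a mismatch between the power statement and the planned test, together with an N that the stated inputs do not reproduce at .05. At α=.025, 126 participants give about 71% to 81% power, with 76% for the average-effect test that the analysis section names as primary. These figures assume a two-sided test, a standardized effect of 0.1 and 42 decision points; the 71% instead takes the stated 80% as correct. The practical effect is modest, because data collection has ended and the achieved sample gives about 80% under the same assumptions. This is a reporting correction worth making before results are interpreted, and not a flaw that threatens the trial.

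**What to change.** In the sample size paragraph, re-derive and restate the power at α=.025 per outcome for the average-effect test, giving its degrees of freedom, sidedness and number of decision points. Label the linear, initial-effect-0 assumption as the planning shape behind the calculator figure, and say which test and α produced 126. If the assumptions used here are confirmed, the figures are about 76% at 126, about 74% at 120 and about 80% at the 137 completers; if the calculator inputs differ, report the figures that follow from them. The cost is one paragraph and probably a slightly less favourable planned power. No change to the analysis and no extra participants are needed.

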## Results

The study commenced on February 9, 2023, and the data collection was concluded on June 13, 2023. Of the 172 eligible participants, 161 (93.6%) decided to participate. Of these 161 participants, 137 (85.1%) completed the first phase of the study. In the qualitative phase, interviews were conducted with 18 participants: 7 (39%) from the high-adherence group, 7 (39%) from the medium-adherence group, and 4 (22%) from the low-adherence group. Currently, the data processing and analyses are being conducted.

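### The target of 200 does not cover the stated 40% dropout: it leaves 120 of the 126 participants required, and covers 37% (minor, one-sentence correction)

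*Protocol article*

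**What the plan says.** The protocol article justifies its sample size in one paragraph (Participants, Phase 1: MRT, Overview). The target comes first: "A total of 200 students at EUR will be recruited". The design inputs are a 21-day intervention period, a 60% probability of being randomized to an exercise, an expected response to prompts entered as "we assume a constant availability of 70" percent, and a linear effect over time "with an average size of 0.1 and an initial effect of 0 at the start of the study". The result follows: "126 participants will generate 80% power to detect the assumed effect with a significance level of .05". The last step is the allowance for attrition: "We will increase the participant number to 200 to account for a dropout rate of 40" percent, a rate the article bases on average attrition in smartphone mental health interventions.

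No other inflation rule, rounding or further allowance is given anywhere in the article. The target of 200 recurs in the Abstract, in Study Design and in both sections on the interview phase. The Results section gives the outcome of recruitment: "Of these 161 participants, 137 (85.1%) completed the first phase of the study".

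**The concern.** The allowance for dropout is meant to ensure that the participants who remain still reach the number the power calculation requires. Here the requirement, the dropout rate and the inflated target stand in adjacent sentences, and the third does not follow from the first two. At the plan's own dropout rate, its own target ends below its own requirement.

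What is at stake is the accuracy of the sample-size justification. A trial report normally restates the planned size and its rationale. If this sentence is repeated unchanged, the report will claim protection against 40% dropout that 200 did not give. The article says analysis is still under way, so the wording can be corrected before then.

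**Working it through.** **Inputs.** All come from the sample-size paragraph, except the number of decision points (Study Design: randomization twice a day, so 2 × 21 = 42) and the actual numbers (Results).

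- Required number: 126, for 80% power at .05
- Dropout: d = 0.40
- Recruitment target: 200
- Actual: 161 enrolled, 137 completed

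**Step 1. Try to reproduce 200 from 126 and 40%.**

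- Standard rule, n/(1 − d): 126/0.60 = 210.
- The common but incorrect rule, n × (1 + d): 126 × 1.40 = 176.4, so 177.

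Neither gives 200.

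**Step 2. Work back from 200.**

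- Remaining after 40% dropout: 200 × 0.60 = 120, which is 126 − 120 = 6 short.
- Dropout that 200 can absorb: 1 − 126/200 = 0.37, or 37%.
- Shortfall in recruits: 210 − 200 = 10, or 10/210 = 4.8%.

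**Step 3. Size of the effect on the plan's own basis.** Take the article at its word that 126 gives exactly 80% power at .05. In the usual noncentral-F calculation for a microrandomized trial, the noncentrality is N × c, where c depends on the effect, the availability and the randomization probability. Solve for the c that gives 80% power at N = 126, then change only N:

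| N | Power, one effect parameter | Power, two effect parameters (linear trend) |
|---|---|---|
| 120 | 78.0% | 77.8% |
| 126 | 80.0% | 80.0% |

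The loss is about 2 percentage points, whichever form of test is assumed.

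**Step 4. Is 126 itself a hard threshold?** Using the stated inputs directly, c = 0.70 × 0.60 × 0.40 × Σd_t², with d_t rising linearly from 0 to average 0.1 over 42 decision points. Σd_t² is about 0.57, so c is about 0.095 to 0.096, depending on whether the effect changes by decision point or by day. With two effect parameters at .05, the number needed for 80% power comes out at 103 to 106, and 120 participants have about 86% power. The article's 126 is therefore not reproduced at .05 under these settings. The settings entered in the web calculator are not given, so this is a check on a standard formula and does not show that 126 is wrong.

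**Step 5. What happened.** Dropout was (161 − 137)/161 = 24/161 = 14.9%. The 137 completers exceed 126 by 11.

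**The case against.** Four arguments can be made against giving this point weight.

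- **200 may be a round number.** The article does not say so, and rounding 210 down to 200 removes part of the protection that the sentence claims. This does not rescue the wording.
- **A dropout in this design is not a total loss.** Decision points are the randomized units, so someone who leaves in the second week has already contributed observations. The analysis section also provides for multiple imputation if more than 10% of data are missing. This is fair, and it makes division by 1 − d a conservative rule. But missed prompts are already counted through the 70% availability, and dropout is added as a separate loss. The assumed effect also starts at 0 and grows, so the later observations that a dropout fails to give carry most of the information.
- **The trial is closed and 126 was exceeded.** This stands, and it is why the point is minor. Only the wording remains to be corrected.
- **An actual loss of the 80% target is not shown.** This also stands. With the stated inputs, a standard two-parameter formula gives 120 participants about 86% power at .05.

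A reader might infer that the trial was planned or run with inadequate power. The documents do not support that: the only established fault is a mismatch between stated figures, and the trial ended with 137 completers. A reader might also apply 40% dropout to the 161 actually enrolled and find a larger deficit. That did not happen, since observed dropout was 14.9%. Finally, recalculating power at the Bonferroni-corrected level used in the analysis would mix in a separate question, because the sample-size paragraph states its requirement at .05.

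**Conclusion.** Wrong as written, and minor. A target of 200 does not account for 40% dropout from a requirement of 126: it leaves 120, covers 37%, and 210 would have been needed. This is arithmetic on three stated figures and depends on no modelling assumption.

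The consequence is six expected completers, or about 2 power points (80% to about 78%). That size rests on two assumptions: that 126 gives exactly 80% power at .05, as the article says, and that dropouts contribute nothing, as the article's own allowance implies. If either is relaxed in the directions discussed above, the practical effect shrinks further. The completed trial is not affected on this count.

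**What to change.** Correct the sentence in the sample-size paragraph, and use the corrected form wherever the planned size is justified in the trial report. Either of these would do:

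- a recruitment target of 200 allows for about 37% dropout from the required 126; or
- with 200 recruited, 40% dropout would leave 120 participants, with about 78% power if 126 gives 80% at a significance level of .05.

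The cost is one sentence. The target of 200 can stay as the planned number wherever else it appears. No further enrolment and no change to the analysis are needed.
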